**Phase C: Demagnetised MagnaMaxTM (dummy)**

This device will appear identical to the experimental device, although it will have no magnetic properties. This device should therefore be entirely inert. Participants are likely to realised that device has been demagnetised and therefore view it as a placebo.

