**Case Report Forms**

General practices will be encouraged to report all adverse events or reactions using standard forms provided. Similarly, participants will be asked to report any such events directly to the trial and inform their GP.

- 1. **What is the proposed sample size?**

The sample size for this trial was determined using *GPower* (Erdfelder et al). This suggested that complete data from 62 participants would provide 80% power to detect a minimal clinically important improvement of 20% in pain outcomes (Felson et al 1995) for the full strength device using a one way analysis of variance (P = 0.05). This assumed a mean score of 65 on a standard 100mm pain visual analogue scale (VAS) for the demagnetised device, with a difference of -13 for the full strength device and -6.5 for each of the placebo devices. An upper limit of 21.7mm was set for the common standard deviation within subjects. Estimates for both mean and standard deviation were based on data obtained by the MACROPOD trial, together with data presented by Segal and colleagues (2001).

Allowing for a maximum of 10% attrition from recruitment to final data collection, 69 participants will need to be recruited (refer to Section 3.12).

- 1. **What is the planned recruitment rate?**

216 potentially eligible patients with RA will be approached with information about the trial and invited to take part. Based on experience from the MACROPOD trial and taking into account the fact that blood samples will be required for participation, it is anticipated that roughly 50% (108) of patients will fail to respond.

For those who express an interest, a meeting will then be arranged. Patients will be sent an appointment letter together with a copy of the consent form and a baseline questionnaire. During the meeting the chief investigator will offer a detailed explanation of the trial, show examples of the devices involved and answer any questions. He will then assess eligibility, seek the patients’ written consent to participate in the trial and collect the baseline questionnaire. Meetings will normally take place within the patient’s home as a pill count will also be conducted if the person is recruited. At this stage it is estimated that up to 35% (38) patients will either be found to be ineligible or decline to participate. This should leave 69 patients who will then be entered into the trial.

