Up to 12 general practices will be recruited in two phases. Initially the trial will seek to recruit nine large general practices over a period of one month from three primary care trusts: 1) Hull PCT; 2) East Riding of Yorkshire PCT; 3) Selby & York PCT. Practices approached will be those with four or more partners. This will help to ensure the availability of a practice nurse or phlebotomist at each site for the purpose of taking blood samples. Roughly equal numbers of patients with RA will then be contacted by each practice to help achieve a fairly representative sociodemographic cross section of this clinical population. Should the nine practices fail to identify a sufficiently large number of patients with RA, then an additional three practices will be recruited.

- 1. **Give details of the planned analyses**

Data from all participants recruited into the trial will be included in the analysis according to intention to treat. The basic statistical method used for the purpose of primary analysis will be that of analysis of variance. This will look for a significant difference in treatment outcomes amongst the four devices using follow up scores from each treatment phase. If magnet therapy of any true therapeutic benefit one would expect this to show a statistically significant difference between devices in favour of better outcomes for the experimental (full strength MagnaMax) device. However if a significant difference is observed with poorer outcomes for the demagnetised dummy device then the other three devices, then this would tend to indicate that any benefit of magnet therapy may be attributed simply to a placebo effect. This assumes that both attenuated and copper bracelets serve as valid placebos, which is an issue that will be explored in greater detail. Within this analysis a significant difference in treatment effects for the pain VAS (as the primary outcome measure) will be viewed as the critical test.

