As a secondary step in the analysis, estimated treatment effects for each of the devices will also be adjusted according to medication use and compliance, for both of which continuous data will be available. The assumption here is that both of these variables are likely to modify the effects of treatment in terms of all major outcomes. Specifically it is believed that a reduction in either of these variables is likely to reduce the apparent effectiveness of magnet therapy. In pragmatic terms this may not be important, however for the majority of readers this may be interest. The basic approach used for this purpose will be that of multiple regression, testing first for non-linear relationships (Bland 2000).

Further refinement to analysis plan will be sought towards completion of the data collection stage of this trial. This will take into consideration advice from [name] and may involve adjusting for possible period effects as described using a ‘basic estimators approach’ outline in Section 5.4.1 of *Crossover Trials in Clinical Research 2ed* (Senn 2002)

Treatment effect estimates will be presented for each of the four devices together with their standard error and 95% confidence intervals. The computer package used for this purpose will be SPSS® and possibly also SAS®.

- 1. **Are there any planned subgroup analyses?**

Further analyses will be performed in order compare effects according to age, sex and primary location of pain. Differences in effect according to treatment preference will also be explored. The focus here will be on identifying possible baseline variables which may serve as useful predictors of treatment effectiveness, although dangers associated with multiple testing will be acknowledged. Similarly, this trial will explore a number of factors in terms of their possible role in mediating observed placebo effects. These will include level of education, belief in holistic and complementary medicine and belief in the paranormal. The latter of which will be measured at baseline using the HCAMQ (Hyland et al 2003) and Australian Sheep-Goat Scale (Thalbourne 2001).

- 1. **What is the proposed frequency of analyses?**

Analysis will be performed at the end of the trial only, although adverse events and reactions will be actively monitored.

- 1. **Will the trial address any economic issues?**

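### The critical test on pain is a global four-device ANOVA whose two stated readings overlap, so the pattern the trial was sized to find counts both as true benefit and as placebo effect

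*Protocol*

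**What the plan says.** The section on planned analyses (Protocol, section 3) states: "The basic statistical method used for the purpose of primary analysis will be that of analysis of variance". It continues: "This will look for a significant difference in treatment outcomes amongst the four devices using follow up scores from each treatment phase". On the pain VAS, "a significant difference in treatment effects for the pain VAS (as the primary outcome measure) will be viewed as the critical test".

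Two patterns are then interpreted:

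- **Benefit reading.** If the magnet truly works, the authors expect a "statistically significant difference between devices in favour of better outcomes for the experimental (full strength MagnaMax) device". The comparator for full strength is not named.
- **Placebo reading.** After a 'However', the text considers what follows "if a significant difference is observed with poorer outcomes for the demagnetised dummy device then the other three devices". This would tend to point to a placebo effect, provided that the attenuated and copper devices are valid placebos.

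The sample size section uses a one-way ANOVA at P = 0.05 with 62 completers for 80% power. It assumes a mean of 65 mm on the demagnetised device, "with a difference of -13 for the full strength device and -6.5 for each of the placebo devices", and a within-subject SD of up to 21.7 mm.

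The description of the demagnetised device adds: "Participants are likely to realised that device has been demagnetised and therefore view it as a placebo". For reporting, "Treatment effect estimates will be presented for each of the four devices together with their standard error and 95% confidence intervals".

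**The concern.** The principal question is whether the magnet has a true effect on pain beyond placebo. A test with 3 numerator degrees of freedom for any difference among four devices does not ask that. It rejects whichever device stands apart, including when only the dummy is worse. The protocol foresees that case, because it expects participants to recognise the dummy.

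The conclusion therefore rests on the two readings. They would suffice if they were exclusive, or if one took precedence. They are not exclusive: when full strength does best and the dummy does worst, both apply. That ordering is also the one assumed for the sample size. A trial that found exactly what it was designed to find could be reported either as true benefit or as placebo effect.

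The reporting sentence does not settle this, since it commits to estimates for each device and not to differences from full strength.

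**Working it through.** **Inputs.** From the sample size section: means full strength 52 (65 − 13), attenuated 58.5 and copper 58.5 (65 − 6.5), demagnetised 65; SD 21.7; n = 62; alpha 0.05. Assumptions made here: equal variances and correlations across devices; full strength counts as favoured when its mean is numerically best; the dummy counts as worse than the others when its mean is numerically worst.

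**1. The plan's own figure.**

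- Grand mean = 58.5. Sum of squared deviations = 6.5² + 0 + 6.5² + 0 = 84.5.
- Effect size f = √(84.5/4)/21.7 = 0.212.
- Noncentrality = 62 × 84.5/21.7² = 11.13.
- Power, one-way (df 3, 244) = 0.802. Power, within participants (df 3, 183) = 0.800.
- Recruitment: 62/0.90 = 68.9, so 69.

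The stated 62 and 69 are reproduced. The sample size arithmetic is not at fault.

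**2. Overlap under the planning scenario.** Device means were simulated as normal with SE 21.7/√62 and an independent error variance on 183 df (at least 200,000 trials per scenario).

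| Outcome | Share of all trials |
|---|---|
| F significant | 80% |
| Significant, full strength best | 75% |
| Significant, dummy worst | 75% |
| Significant, both | 70% |

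About 0.695/0.799 = 87% of significant trials meet both readings.

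**3. What each order of precedence would imply.**

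- *Placebo reading overrides.* A true effect of the planned size is attributed to placebo in about 70% of trials, counting those where both readings apply.
- *Benefit reading overrides.* Take a pure placebo effect: the dummy is worse by a gap and the other three are equal. The gaps are borrowed from the protocol's own differences.

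| Gap | F significant | Also full strength best | Of those, dummy also worst | Full strength best, dummy not worst (all trials) |
|---|---|---|---|---|
| 6.5 mm | 37% | 12% | 96% | 0.45% |
| 13 mm | 94% | 31% | over 99.9% | 0.02% |

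The 12% and 31% are close to one third of the significant trials, as expected when three equal devices compete for first place.

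**4. A contrast that separates the two.** Specific effect = full strength minus the mean of attenuated and copper.

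- Variance factor 1 + ¼ + ¼ = 1.5, so SE = 21.7 × √(1.5/62) = 3.38 mm.
- At the planned 6.5 mm: 6.5/3.38 = 1.93, against a critical t of 1.97 on 183 df. Power is 48% (46% if the F test must also be significant).
- Under a pure placebo effect the contrast is zero. It falsely favours full strength in about 2.5% of trials at either gap.
- For comparison, full strength against the dummy (13 mm) has 91% power, but a placebo effect alone produces that difference too.

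**The case against.** A reader might infer that the protocol would report a pure placebo effect as magnet benefit in 12% to 31% of trials. The text does not support that. A worse dummy with the other three alike is exactly the pattern that the protocol attributes to placebo, and that reading also applies in 96% to over 99.9% of the trials counted. Those percentages become error rates only if the benefit reading overrides and 'in favour of' means numerically best. The protocol states neither.

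Other points on the authors' side:

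- The benefit reading is worded as what one would expect if the magnet works, not as a rule of inference. The placebo reading is hedged and conditional on valid placebos. This stands, but the sentence naming the critical test carries no hedge.
- If 'However' gives the placebo reading precedence, false benefit claims fall below 1%. The error then runs the other way: about 70% of trials with a real effect of the planned size would be read as placebo.
- Follow-up contrasts are often left to an analysis plan, and the protocol promises later refinement, with the code concealed from the chief investigator until data collection ends. This stands in part. Missing contrasts would not be a finding in themselves. Here, though, the protocol itself fixes the critical test, sizes the trial on it and states overlapping readings. The only refinement it mentions is adjustment for period effects.
- Participants' guesses about each device will help interpretation. They do not decide which reading applies.

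**Conclusion.** The concern holds as an ambiguity in the primary decision. The global test cannot by itself separate true benefit from placebo effect. The two readings offered to do so are not exclusive, have no stated precedence, and both fit the planning means. At the planned effect both apply in 70% of all trials and 87% of significant ones. Whichever reading is put first, a foreseeable scenario is misread.

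These figures rest on the protocol's SD of 21.7 mm, 62 completers, equal variances and correlations, and numerical ranking as the meaning of better and worse. The pure placebo gaps of 6.5 and 13 mm are assumptions. The documents do not support a definite false-benefit rate for the rule as written, nor any error in the sample size calculation.

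**What to change.** Keep the four-device F test on the pain VAS as the first step, and replace the two readings with pre-specified within-participant contrasts:

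1. Specific effect: full strength minus the mean of attenuated and copper.
2. Placebo effect: dummy minus the mean of attenuated and copper.

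Report both as differences with 95% confidence intervals. Claim benefit beyond placebo only if the first is significant two-sided at 5%. Because the protocol allows that the weak magnet may have some action and leaves the validity of copper as a placebo open, also show full strength against each of the two separately. The false-benefit rate of about 2.5% holds only if both comparators are inert and as credible as full strength.

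The text should be settled before the code is released. No new data are needed and no change in enrolment is proposed. There is a real cost, and the protocol should state it: a significant F test alone would no longer support a benefit claim, the 80% power belongs to that F test, and the specific-effect contrast has about 48% power at 6.5 mm with 62 completers. A non-significant contrast should therefore be reported through its confidence interval and not as proof that the magnet has no effect.

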Whilst results presented by Segal and colleagues may be challenged on the basis of poor trial design and lack of statistical power, this study nevertheless highlights a number of other methodological weaknesses which characterise other published trials of magnet therapy. Importantly, medication use was not measured although participants were likely to alter their use of analgesics as a response to changes in pain intensity. Any true benefit derived from magnet therapy may therefore have been masked by a reduction in medication use. Trials of magnet therapy should also give participants the opportunity to use devices in a manner which reflects common practice within the real world. Since magnet therapy is generally understood to involve prolonged periods of exposure to magnetic fields, it may be argued that short periods of exposure will prove insufficient for any cumulative therapeutic effect to occur. In the case of the trial described above, an exposure period of one week may well have been inadequate. Certainly compliance should also have been reported since there is no guarantee that trial participants actually wore the devices as recommended. Even if analysis of data is by intention to treat rather than by active treatment, this information will still be of value.

Perhaps the greatest methodological challenge faced by trial of magnet therapy however is that of providing adequate control devices against which any ‘true’ effects from magnet therapy may be assessed. RCTs which incorporate a placebo control group are generally perceived as methodologically superior to those which do not. This is especially the case for trials involving new treatments and subjective outcome measures (Avenell et al 2004, Fergusson et al 2004). The key methodological advantage of placebo controlled trials over open trial designs relates to the ability to blind participants, clinicians and researchers to the allocation of experimental and control treatments (Vickers and de Craen 2000). This helps to avoid systematic bias resulting from differences in the perceived or desired effectiveness of treatments which may alter the outcomes being assessed (Schulz and Grimes 2002, Campbell 2003, Akobeng 2005).

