For the proposed trial three of these measures would require repeated physical assessment by a suitably qualified clinician, generally speaking a rheumatologist. However this is neither feasible nor warranted. Indeed, Pincus (2005) has shown that a pooled index of the three self-report measures may discriminate equally well to the ‘core set’ in terms evaluating the efficacy of treatments in placebo controlled trials. Perhaps more importantly however the primary focus of this trial is on the effects of magnet therapy on pain and inflammation in RA rather than overall disease activity. As such, the primary outcome measure should be pain specific.

For the present trial a 100mm pain visual analogue scale (VAS) was selected, as consistent with the recommended method of pain measurement according to ACR criteria. This displays verbal anchors indicating “no pain” at one end to “worst pain ever” at the other. Visual analogue scales have been widely used for quantifying pain for a range of conditions including rheumatoid arthritis and have been shown to be adequate for this purpose in terms of reliability, validity and sensitivity (Malaise and Franchimont 1987, Duncan 1989, Bellamy et al 1999). The McGill Pain Questionnaire will be used as a second pain outcome measure, as this covers affective components and may also be used to validate findings from the VAS. This will also aid comparison of findings with studies reported elsewhere.

Possible variation in participants’ use of medication may have a confounding effect on pain outcomes. This will have the tendency of reducing any otherwise observable difference between groups resulting from a true treatment effect. Medication use during each treatment phase will therefore be quantified. This will enable pain outcomes to be adjusted if necessary on the basis of regression analysis. Whilst the main emphasis will be placed on measuring changes in the use of prescribed analgesic drugs (e.g. co-codamol and paracetamol), it is important to note that use of other drug types (e.g. NSAIDs) will have an impact on pain and therefore will be accounted for also.

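### Regression adjustment for analgesic use and compliance, both measured after allocation, does not estimate the device effect at equal medication

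*Protocol*

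**What the plan says.** The primary analysis, in the protocol section on planned analyses, is an intention-to-treat analysis of variance of the follow-up scores from each phase, with the pain VAS as the deciding outcome. The same section then adds a secondary step in which "estimated treatment effects for each of the devices will also be adjusted according to medication use and compliance". On method it says: "The basic approach used for this purpose will be that of multiple regression". The reason given is a belief that "a reduction in either of these variables is likely to reduce the apparent effectiveness of magnet therapy".

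The section on outcome measures makes the same plan for pain after explaining that drug use in each phase will be quantified: "This will enable pain outcomes to be adjusted if necessary on the basis of regression analysis".

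Four other places bear on what kind of variables these are:

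- The background section, criticising an earlier magnet trial in rheumatoid arthritis, says "participants were likely to alter their use of analgesics as a response to changes in pain intensity", and that "Any true benefit derived from magnet therapy may therefore have been masked by a reduction in medication use".
- The secondary research questions list analgesic use among the outcomes on which the device is to be judged.
- The pill-count section has tablets counted at recruitment and at the end of each phase. Drug use is thus estimated per phase, after allocation.
- The section on problems with compliance regards failure to wear a device as an outcome in itself.

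**The concern.** The outcome-measures section treats medication as a confounder of pain. The background section makes it a consequence of pain. Both can be true, and then ordinary covariate adjustment does not deliver what the protocol wants from it.

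Within one patient, a bad phase raises both the VAS and the tablet count. Drug use in a phase therefore carries information about that phase's pain, including whatever part of the pain the device changed. Comparing devices at equal drug use removes some of the device effect along with the masking. Random sequences and within-patient comparison do not prevent this, because the shared cause is phase-to-phase fluctuation inside the patient.

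At stake is interpretation. The protocol expects adjustment to restore an effect hidden by reduced drug use. The adjusted figure could instead lie further from the true effect than the unadjusted one, and nothing in the text warns the reader of that.

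**Working it through.** **The plan's own figure.** The sample-size section gives means of 65 (demagnetised), 52 (full strength, 13 lower) and 58.5 twice (6.5 lower), with SD 21.7. The grand mean is 58.5 and the deviations are 6.5, -6.5, 0 and 0. Hence f = sqrt(84.5/4)/21.7 = 4.596/21.7 = 0.212. A one-way analysis of variance on four devices at 0.05 first reaches 80% power at n = 62 (power 0.802), and 62/0.9 = 68.9, so 69 recruited. Both stated figures reproduce. They do not involve the adjustment.

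**Model for the adjustment.** From the protocol: tau = -13 mm, used as an illustrative true effect at equal medication. Assumed, because the protocol gives no values: a (how strongly pain drives drug use), b (how strongly drug use lowers recorded pain) and r.

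- Pain tendency in a phase: L = tau·D + e, where D marks the device
- Drug use: M = a·L + u
- Recorded pain: Y = L - b·M, plus independent error

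**Unadjusted effect.** Substituting M gives Y = (1 - ab)L - b·u. The device difference is tau(1 - ab), so ab is the share masked.

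**Adjusted effect.** Given D and M, the expected L is tau·D + k(M - a·tau·D), with k = a·var(e)/(a²·var(e) + var(u)). The product a·k equals r², the squared correlation of L and M within device. The coefficient of D with M held fixed is therefore tau(1 - r²).

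**Comparison.** Adjusted minus unadjusted = tau(ab - r²). Adjustment is worse than none when r² > ab and better when r² < ab. It recovers tau only when r = 0.

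| Share masked (ab) | Unadjusted, mm | Adjusted, r² = 0.05 | r² = 0.1 | r² = 0.2 | r² = 0.3 | r² = 0.5 | r² = 0.7 |
|---|---|---|---|---|---|---|---|
| 0.1 | -11.7 | -12.35 | -11.7 | -10.4 | -9.1 | -6.5 | -3.9 |
| 0.2 | -10.4 | -12.35 | -11.7 | -10.4 | -9.1 | -6.5 | -3.9 |
| 0.3 | -9.1 | -12.35 | -11.7 | -10.4 | -9.1 | -6.5 | -3.9 |
| 0.5 | -6.5 | -12.35 | -11.7 | -10.4 | -9.1 | -6.5 | -3.9 |

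The adjusted value does not depend on ab, so the rows repeat; what changes is the figure it must beat.

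**Simulation.** With 62 patients, four phases, within-patient SD 21.7 before the drug response and half of that variance taken as felt pain, within-patient regression agreed with these values to about 0.5 mm in every cell. When drug use shared no cause with phase pain except the device (20% masking), adjustment came close to the true effect: -12.8 mm, against -10.4 mm unadjusted. With no device effect, both estimates were about zero.

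**The case against.** The strongest reply is that little hangs on this. The primary test is unadjusted, and the protocol calls the adjustment a secondary step that may not matter in pragmatic terms. It also leaves the analysis plan open to later refinement. That limits the consequence. It does not remove the point, because the protocol already names the method and both covariates, and the only refinement it specifies concerns period effects.

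A second reply is that adjustment may help. It does in part of the table: with 30% masking and r² = 0.2 the adjusted effect is -10.4 mm against -9.1 mm unadjusted. This stands in full. A reader might infer that adjustment will hide more of a real effect than drug use does. The documents do not support that, since they give no value for r or ab.

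Three further inferences also go too far:

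- **That wearing time is biased in the same way.** This needs patients to wear a device longer when it relieves pain. The protocol does not say so and expects compliance to be unproblematic. What it does support is that wearing time is a post-allocation variable and an outcome.
- **That the protocol's talk of effect modification is at odds with its regression.** The text does not restrict the model to main effects, and interaction terms may properly be settled in a statistical analysis plan.
- **That a combined pain-and-medication score is needed.** In simulation under this model, at r = 0.3 and ab = 0.1, a rank-sum composite had power 0.56, against about 0.75 for either the unadjusted or the adjusted analysis.

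**Conclusion.** The point holds for the meaning of the adjusted estimate. On the protocol's own account drug use responds to pain. The medication-adjusted coefficient then falls short of the effect at equal medication by a fraction r², and is not the unmasked magnet effect. At the protocol's 13 mm, r² of 0.1, 0.3 and 0.5 give shortfalls of 1.3, 3.9 and 6.5 mm.

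These sizes rest on a linear model in which the device reaches drug use only through pain, and on assumed values of r². Whether the adjusted figure is better or worse than the unadjusted one in this trial cannot be told from the document. The finding of no bias under a null device rests on the same model. The primary analysis of variance, the 62 completers and the 69 recruits stand as they are.

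**What to change.** In the sections on outcome measures and planned analyses, stop presenting covariate-adjusted figures as device effects. Instead:

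1. Analyse analgesic use per phase as an outcome, with the same crossover model as the VAS, and report it beside the unadjusted VAS effect. A reader can then see whether similar pain was reached with fewer tablets.
2. Report wearing time by device.
3. If the adjusted regression is kept, label it exploratory and conditional on variables measured after allocation, and state that it does not estimate the unmasked or direct effect of the magnet.

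The cost is wording only. Pill counts, prescription records and reported wearing time are already to be collected, and analgesic use is already a secondary outcome. The small downside is that readers are not offered a single medication-adjusted effect.

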**Phase D: Copper bracelet (placebo)**

Participants will also test a commercially available copper bracelet. As copper bracelets are widely used for pain relief by the general public it is likely that participants may expect this to have some therapeutic benefit. Whether or not this device actually represents a valid placebo is a question which will be addressed as part of the trial.

Participants will be asked to wear each of these devices for a minimum of 12 hours per day, although ideally they should be worn continuously.

- 1. **What are the proposed practical arrangements for allocating participants to the trial groups?**

Participants will randomly allocated to 1 of 24 possible treatment sequences. Treatment sequences will consist of four phases, with each phase corresponding to a particular device (as shown in Appendix 1). This method is preferred over the use of a Latin square design, as this will help to minimise possible analytical bias associated with attrition.

Randomisation will be performed remotely and independently by the York Trials Unit using a relevant computer programme to avoid any bias in sequence allocation. Block randomisation will be unnecessary. The randomisation code will be will be concealed from the chief investigator until all data collection has been completed. Once the full randomisation sequence for all potential participants has been determined, then devices will be packed and sealed in identical padded boxes, distinguishable only by a trial ID number and order in which they are to be distributed.

- 1. **What are the proposed methods for protecting against other sources of bias?**

Several additional methods will be employed to counter potential threats from bias in terms of both the internal and external validity.

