**Inclusion criteria**

- 18 years of age or over
- Diagnosis of rheumatoid arthritis within medical records
- Currently prescribed analgesic medication
- Chronic pain: either persistent or intermittent over a minimum period of three months prior to recruitment (Argoff 2002)
- Current pain: greater than 30/100mm on VAS within the last 24 hours despite medication.

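### The primary analysis of variance should fit period as a factor; the protocol leaves this optional while allocating 69 people to 24 sequences without restriction

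*Protocol*

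**What the plan says.** All references are to the protocol.

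- **Allocation** (section on practical arrangements for allocating participants): participants are "randomly allocated to 1 of 24 possible treatment sequences". The same section says "Block randomisation will be unnecessary" and describes no other restriction on sequence. The list is made in advance: "Once the full randomisation sequence for all potential participants has been determined, then devices will be packed and sealed".
- **Primary analysis** (section on planned analyses): "The basic statistical method used for the purpose of primary analysis will be that of analysis of variance". It compares follow-up scores from each phase among the four devices. Device is the only factor named.
- **Period** (same section): "Further refinement to analysis plan will be sought towards completion of the data collection stage of this trial", and this "may involve adjusting for possible period effects", citing a basic estimators approach from a crossover textbook.
- **Concealment** (allocation section): the code is "concealed from the chief investigator until all data collection has been completed".
- **Wash-out periods**: this section relies on randomisation and a one-week gap against carry-over. It does not mention period effects.

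**The concern.** Listing all 24 orders of four devices balances devices over periods only if the orders are used about equally often. Simple randomisation of 69 people will not achieve that. Each device then sits more often in some periods than in others. If pain drifts over the 23 weeks, part of the drift enters the unadjusted device means, and the rest goes into the residual of an analysis with no period term.

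At stake are the realised full-strength contrasts and the power of the test that the protocol calls critical. The sample size has no slack to absorb a loss. A period term removes the problem, yet the protocol leaves it as a possibility to be settled late in data collection.

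**Working it through.** **1. Reproduce the stated sample size.** Inputs from the sample size section: means 65 (demagnetised), 52 (full strength), 58.5 (attenuated), 58.5 (copper); SD 21.7 mm; alpha 0.05; 80% power.

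- SD of the four means = 4.596, so f = 4.596/21.7 = 0.2118.
- One-way analysis of variance, error df 4(n−1): 80% is first reached at n = 62 (power 80.2%).
- Within-participant analysis, error df 3(n−1) = 183: power at 62 is 79.95%.
- 62/0.90 = 68.9, giving 69. The protocol's figures reproduce. The within-participant value of 79.95% is the baseline below.

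**2. How uneven is the allocation?** With simple randomisation of 69 to 24 sequences:

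- Expected unused sequences: 24 × (23/24)^69 = 1.3. By simulation, the most-used sequence gets 6.6 people on average.
- Each device-by-period cell expects 69/4 = 17.25 people, with SD √(69 × 0.25 × 0.75) = 3.6. By simulation, the largest of the 16 cells averages about 24 and the smallest about 11.
- In 10,000 simulated allocations none had all 16 cells within one of each other. Exact balance is impossible anyway, since neither 69 nor 62 divides by 4.

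**3. Offset in full strength minus demagnetised if period is omitted.** Assume linear drift of t mm per period, so total drift over four phases is 3t. The difference in period position between two devices has mean 0 and variance 2(3×1 + 2×4 + 1×9)/12 = 10/3 per participant. Hence offset SD = t√(10/(3N)), which at N = 69 is 0.22t.

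The contrast standard error without drift is 21.7√(2/69) = 3.69 mm.

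**4. Residual and power if period is omitted.** The residual variance becomes 21.7² + (5/3)t², where 5/3 is the sample variance of 0, 1, 2, 3. Power is for N = 62 with 183 error df.

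| Assumed total drift (mm) | t (mm/period) | Offset SD, N = 69 (mm) | Residual variance ratio | Power at 62 |
|---|---|---|---|---|
| 0 | 0 | 0 | 1.00 | 80.0% |
| 6 | 2 | 0.4 | 1.01 | 79.3% |
| 10 | 3.33 | 0.7 | 1.04 | 78.2% |
| 15 | 5 | 1.1 | 1.09 | 76.1% |
| 30 | 10 | 2.2 | 1.35 | 65.7% |

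**5. Type I error.** The offset variance, t² × 10/(3N), equals (2/N) × (5/3)t², which is exactly what the larger residual adds to the contrast variance. The unadjusted test should therefore keep its size over the randomisation. Simulation (4,000 runs, N = 62) agrees: 0.051, 0.051, 0.049 and 0.053 at t = 0, 2, 5 and 10.

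**6. With period fitted.** Additive period effects drop out whatever the allocation.

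- Losing 3 error df (183 to 180) moves power from 79.95% to 79.94%.
- Unrestricted allocation also makes device and period slightly non-orthogonal. Period-adjusted efficiency is 98.5% on average, so the noncentrality falls from 11.126 to 11.126 × 0.985 = 10.959 and power to about 79.3%.
- Simulated adjusted power at t = 0, 2, 5 and 10 was 0.799, 0.793, 0.785 and 0.785. Unadjusted power was 0.802, 0.799, 0.755 and 0.655. Simulation error is about √(0.8 × 0.2/4,000) = 0.006.

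Adjustment therefore roughly breaks even at 6 mm total drift and gains beyond it.

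**7. Blocks of 24.** Since 69 = 2 × 24 + 21, each sequence is used 2 or 3 times. Period-adjusted efficiency rises from 98.5% to 99.9% before attrition. Without adjustment, at 10 mm total drift, the offset SD falls from 0.73 to about 0.14 mm, or about 0.28 mm once 10% attrition is allowed for.

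**The case against.** **The effect is modest.** At an assumed 10 mm total drift, the offset SD of 0.73 mm raises the contrast standard error only from 3.69 to √(3.69² + 0.73²) = 3.77 mm, about 2%, against a planned difference of 13 mm. This stands. The loss becomes appreciable only at about 15 mm or more.

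**Drift is not shown to be likely.** A reader might infer it from the entry criterion, pain "greater than 30/100mm on VAS within the last 24 hours despite medication", through regression to the mean. But the primary analysis uses follow-up scores only, and the first comes after five weeks of treatment. Most of that regression would precede the first analysed score. The protocol states no drift, so every drift figure here is an assumption.

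**The protocol foresees period effects.** It names them and a method, and has a statistical advisor. Exact model terms may also be settled in an analysis plan that is not shown. That is fair, and it limits the point to the wording: as written, the primary model has no period term and the adjustment is only a possibility.

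**The late decision is not data-driven.** A reader might infer that the model could be chosen on device results. The refinement is placed towards the end of data collection, while the code is still concealed from the chief investigator, so the text does not support that reading.

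**Blocking is not essential.** Once period is fitted, unrestricted allocation keeps 98.5% efficiency. Declining to block is defensible if the model is fixed.

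**Conclusion.** The point holds as one of precision and of firm wording. Following the protocol's text gives an uneven device-by-period layout and a primary analysis that need not account for it. Any drift then puts a chance offset into the realised contrasts and lowers power, from 80.0% to between 79.3% and 65.7% over assumed total drifts of 6 to 30 mm.

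It is not systematic bias. The offset averages zero over the randomisation and the test keeps its 5% level, so a reading that drift would produce false positive findings is not supported.

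The figures assume linear drift common to all participants, the protocol's SD of 21.7 mm as the within-participant residual, and 62 complete cases for power. A smaller within-participant SD would make the same drift matter relatively more.

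**What to change.** **Main change.** In the planned analyses section, replace "may involve adjusting for possible period effects" with a statement that the primary analysis of the pain scale fits participant and period as factors alongside device. This removes additive period effects whatever sequences are drawn. It costs one sentence and three error degrees of freedom, plus the small non-orthogonality loss shown above if allocation stays unrestricted.

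**Optional and minor.** Replace "Block randomisation will be unnecessary" with allocation in permuted blocks of 24. The trials unit draws up the whole list before packing sealed boxes, so this is a change of setting, and a block of that length is hard to predict. It recovers most of the 1.5% efficiency loss before attrition, but cannot give exact balance at 69.
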